#### Sample size

The sample size calculation is based on the primary endpoint: a metabolic acidosis incidence of about 2.8% can reasonably be assumed, as this was previously reported in an observational study conducted in one of the participating centres [11]. Since this will be the first trial to evaluate the effect of computer analysis of intrapartum fetal monitoring signals and real-time alerts on perinatal outcomes, it is not possible to find an estimate of the degree of change that is expected. The closest available parallel is the evaluation of STAN^®^ monitoring versus conventional CTG during labour. A systematic review of the first three trials that studied this issue revealed an overall relative risk for metabolic acidosis of 0.64. In the absence of a better alternative, this will be the value used for initial sample size calculation. Thus assuming a reduction in metabolic acidosis from 2.8% to 1.8%, with an alpha of 0.05, a two-sided test, and a power of 0.80, about 7320 women will need to be randomised. Accounting for a 10% loss to follow-up, the study requires the inclusion of 8133 women in order to obtain the 7320 analysable cases (3660 per arm). A pilot analysis will be conducted after enrolment of the first 1500 cases to evaluate the real incidence of metabolic acidosis, the effect of real-time alerts on its rate, and the need to recalculate the trial's sample size.

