#### Randomisation

After enrolment, women will be randomised to one of two arms using a 1:1 computer-generated randomisation sequence attributed to each centre by the Omniview-SisPorto^®^ 3.5 program.

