#### Data analysis

Data analysis will be carried out at the co-ordinating centre and analysis of the primary endpoint will follow the intention to treat principle. Minimal differences between groups are expected in baseline patient characteristics. The incidence of metabolic acidosis will be compared across both groups, using relative risk with 95% confidence intervals. A similar methodology will be applied to secondary outcomes.

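### The 1500-woman pilot plans a between-arm look at the primary endpoint beside a sample-size decision, with the full 5% kept for an unadjusted final analysis

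*Protocol article*

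**What the plan says.** The Sample size section of the protocol article takes a control incidence of 2.8% from an observational study in one participating centre. It says no estimate of the expected effect is available and borrows one from a systematic review of ST-analysis trials, which "revealed an overall relative risk for metabolic acidosis of 0.64". It adds: "In the absence of a better alternative, this will be the value used for initial sample size calculation". The calculation is made "with an alpha of 0.05, a two-sided test, and a power of 0.80" and gives 7320 analysable women (3660 per arm), or 8133 randomised after 10% loss.

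The section ends with a pilot analysis after the first 1500 women. It has three listed purposes: the real incidence of metabolic acidosis, "the effect of real-time alerts on its rate, and the need to recalculate" the sample size.

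The Data analysis section states that "Data analysis will be carried out at the co-ordinating centre" and that the arms will be compared "using relative risk with 95% confidence intervals". The section on the Data Safety Monitoring Committee covers serious adverse events and does not mention the pilot. The article does not say that the first 1500 women are left out of the final analysis.

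**The concern.** The second purpose of the pilot is a comparison of the primary endpoint between arms, and the sentence ends in a decision about sample size. Since 0.64 is described as a stopgap for an initial calculation, the natural reading is that the effect seen in the pilot may replace it.

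Two things are at stake. First, when the final sample size depends on the interim effect and the same women enter an ordinary final test, that test no longer has exactly its nominal error rate and the 95% interval no longer has exactly its nominal coverage. Second, a sample size taken from the effect seen in so few events would mostly reflect chance. Checking the 2.8% assumption, which is the legitimate need, does not require a comparison of the arms.

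**Working it through.** **Inputs.** From the Sample size section: control rate 2.8%, relative risk 0.64 (intervention rate 0.028 × 0.64 = 1.792%), two-sided alpha 0.05, power 0.80, loss 10%, pilot of 1500 women. From the Randomisation section: "1:1 computer-generated randomisation sequence". The pilot therefore has 750 per arm, or 675 analysable per arm after 10% loss.

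**1. The plan's own figure.** Per arm, n = [1.96√(2p̄(1−p̄)) + 0.842√(p₁(1−p₁) + p₂(1−p₂))]² / (p₁−p₂)². With p₁ = 0.028 and p₂ = 0.01792, n = 3464.6. The continuity correction, (n/4)[1 + √(1 + 4/(n|p₁−p₂|))]², gives 3660.3 against the stated 3660. Then 7320/0.9 = 8133.3 against the stated 8133. The stated size reproduces, so the defect lies in the pilot.

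**2. Precision of the pilot effect at 675 per arm.**
- Expected events: 675 × 0.028 = 18.9 and 675 × 0.01792 = 12.1.
- SE(log RR) = √(1/18.9 + 1/12.1 − 2/675) = 0.364.
- 95% interval around 0.64: 0.64 × exp(±1.96 × 0.364) = 0.31 to 1.31.
- If the true relative risk is 0.64, 12.5% of pilots show no benefit (exact binomial).
- If there is no true effect, about 9% of pilots show a relative risk of 0.643 or less.
- Power for the design effect is 23%. With no loss (750 per arm) it is 25%.

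**3. Sample size implied by the pilot.** The formula in step 1, without continuity correction, was applied to the rates observed in simulated pilots of 675 per arm with a true relative risk of 0.64. The quartiles of total N are about 2,900, 6,500 and 24,000 when pilots pointing towards harm are sized by their absolute difference. Among pilots that show benefit, they are about 2,650, 5,450 and 14,400.

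**4. Type I error if the observed effect alters N.** Equal rates in both arms (1.8%, 2.3% or 2.8%), pilot of 675 per arm, N re-estimated from the observed rates for 80% power, pilot women retained, unadjusted two-sided z-test at the end, and a cap of 2 or 3 times 3660 per arm:

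| Rule | N set from absolute difference, either direction | Planned N kept if the pilot shows no benefit |
|---|---|---|
| N may only rise | 5.5-5.7% | 5.2-5.3% |
| N may rise or fall (floor 675 per arm) | 7.6-7.8% | 6.2-6.3% |

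**5. Type I error under pooled re-estimation.** With N set from the combined incidence and the relative risk fixed at 0.64, the same simulation gives 5.0%.

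**The case against.** The strongest reply is that the rule is inferred. The sentence lists incidence, effect and recalculation side by side, and it can be read as recalculating from incidence with the effect merely reported. This stands in part. The article never says that the effect sets N, and if only pooled incidence did so the error rate would be essentially unaffected. But the article commits to the comparison inside a sample-size decision, and it calls 0.64 provisional.

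A second reply is that this is a condensed article, and that a re-estimation rule, a cap or an alpha adjustment may sit in an analysis plan that is not shown. That is fair as to the missing rule, and the point does not rest on its absence. It rests on what the article does fix: an effect look tied to sample size, beside the full 5% and an ordinary 95% interval at the end. If the analysis plan does adjust, these sentences need to agree with it.

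Four stronger readings are tempting, and the documents do not support them:

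- **A type I error of 9.3%.** This applies if the pilot is tested at 5%, success can be claimed there, and the trial is tested again at the end. The plan provides for no efficacy claim or efficacy stop at the pilot.
- **The trial team would know the interim effect.** The article says where the analysis is done. It does not say who sees the pilot result or whether treatment codes are withheld.
- **The pilot effect is pure noise.** At 23-25% power it carries some information, though too little to set N.
- **An upper quartile of about 33,000 for the recalculated N.** That figure appears only if every pilot showing no benefit is counted as needing an infinite trial.

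**Conclusion.** The concern holds in a limited form. The article plans a between-arm look at the primary endpoint beside a decision on sample size and keeps the full 5% for an unadjusted final analysis. Under the natural reading, type I error rises to about 5.2-5.7% if N may only increase and to about 6-8% if it may also decrease. These figures assume that the observed effect alters N, that the pilot women stay in the final analysis, and that the rule resembles those examined. The inflation is modest under the mildest rules and material under the others, and the article does not say which would apply.

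The imprecision of the pilot effect does not depend on that rule. About 31 events cannot distinguish a two-thirds reduction from a 30% increase, so a sample size derived from them would be largely arbitrary. This should be fixed, and settled before the pilot analysis is run.

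**What to change.** Rewrite the last sentence of the Sample size section to say that, after 1500 women:

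- only the pooled incidence is computed, with the arms combined and treatment codes withheld;
- N is recalculated from that incidence with the relative risk fixed at 0.64;
- no between-arm comparison is made for this purpose.

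This still answers the real question. At the design values the pooled rate is about 2.3%, and 2 × 0.023/1.64 returns the 2.8% control rate and an analysable N of about 7,308. With 34 events in 1500, the exact 95% interval for the pooled rate is 1.57% to 3.15%, which corresponds to an analysable N of about 10,780 down to 5,290.

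If a comparative look is wanted for safety, give it to the Data Safety Monitoring Committee only, and state that it can neither change N nor support an efficacy claim.

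The cost is protocol wording. The one loss is that N cannot respond to the observed effect, which at this size is too imprecise to be a useful guide.

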#### Data analysis

Data analysis will be carried out at the co-ordinating centre and analysis of the primary endpoint will follow the intention to treat principle. Minimal differences between groups are expected in baseline patient characteristics. The incidence of metabolic acidosis will be compared across both groups, using relative risk with 95% confidence intervals. A similar methodology will be applied to secondary outcomes.

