## Methods/design

### Study Design and Setting

This is a pragmatic multicentre randomised clinical trial, to be carried out in five United Kingdom hospitals, including three tertiary teaching units and two district general hospitals, all with high-risk women in labour.

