#### Primary outcome measure

The primary outcome measure of this study is the incidence of fetal metabolic acidosis (defined as an umbilical artery pH < 7.05, BD_ecf _> 12 mmol/L). BD_ecf _will be calculated from pH and PCO_2 _values, according to the Siggaard-Andersen acid-base algorithm [18]. Subgroup analysis, by participating centre and by availability or non-availability of ST analysis will be carried out.

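### Allocation is by centre, but the relative risk as written does not carry centre into the overall estimate; stratifying would be a small, free improvement

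*Protocol article*

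**What the plan says.** Randomisation section: women are allocated by a "1:1 computer-generated randomisation sequence attributed to each centre", so centre is a randomisation stratum. Study Design and Setting: the trial is "to be carried out in five United Kingdom hospitals", "including three tertiary teaching units and two district general hospitals".

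Data analysis section: "analysis of the primary endpoint will follow the intention to treat principle", and "The incidence of metabolic acidosis will be compared across both groups, using relative risk with 95% confidence intervals". Secondary outcomes are to be handled in a similar way. No centre term is named, and the relative risk is not called crude or unadjusted either.

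Centre appears once in the planned analyses, under Primary outcome measure: "Subgroup analysis, by participating centre and by availability or non-availability of ST analysis will be carried out".

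**The concern.** When allocation is done separately by centre, the usual practice is to let the overall estimate follow the same strata. There are reasons to expect centres to differ here. The hospitals are of two types. Control-arm care follows each unit's own practice, which may or may not include ST analysis and fetal blood sampling. The one acidosis rate that the article gives comes from a single participating centre.

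If the overall relative risk leaves centre out, one of two things follows. With arms balanced within each centre, the point estimate is unchanged, but the standard error includes between-centre variation that the design has already removed, so the interval is somewhat too wide. With unblocked sequences, the interval is correct, but the estimate carries some avoidable noise from chance imbalance within centres. In both cases the loss is in precision and not in validity. The question is how large it is.

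**Working it through.** **1. The plan's own figure.** Inputs from the Sample size section: "assuming a reduction in metabolic acidosis from 2.8% to 1.8%, with an alpha of 0.05, a two-sided test". The same section sets power at 0.80 and arrives at 7320 before any allowance for loss. The effect size comes from a relative risk of 0.64, and 0.028 × 0.64 = 0.01792.

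- The two-proportion formula with pooled variance, two-sided 0.05 and power 0.80, gives n = 3465 per arm for 2.8% against 1.792%.
- Continuity correction: n/4 × [1 + √(1 + 4/(n·d))]² with d = 0.01008. Here n·d = 34.93, so the factor is (1 + 1.0557)²/4 = 1.0565 and n = 3661 per arm, or 7322 in total. The stated 7320 is reproduced.
- Loss to follow-up: 7320/0.9 = 8133. Also reproduced.

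This is an unstratified calculation, and nothing below changes it.

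**2. How much centre can matter.** Take five equal centres (7320/5 = 1464 women each) and no treatment effect. The share of the variance of the log relative risk that lies between centres is

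f = Var(centre rates) / [p(1 − p)], where p is the mean rate.

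With unblocked sequences, stratifying removes about f of the variance. With exact balance within centres, the Mantel-Haenszel estimate, Σ(aₖn₀ₖ/Nₖ) / Σ(cₖn₁ₖ/Nₖ), has every weight equal to ½. It therefore equals the unstratified relative risk, and there is no gain in the estimate. The unstratified standard error is then too large, and the true type I error is about 2Φ(−1.96/√(1 − f)).

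The documents give no centre-specific rates, so all rates below are assumed.

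| Outcome | Assumed centre rates | Var / p(1 − p) | f | Type I error, unstratified, balanced within centre |
|---|---|---|---|---|
| Acidosis | 1.5, 2.0, 2.8, 3.5, 4.2% | 0.0000956 / 0.027216 | 0.35% | 0.050 |
| Acidosis | 1.0, 1.5, 2.5, 3.5, 5.5% | 0.000256 / 0.027216 | 0.94% | 0.049 |
| Fetal blood sampling | 5 to 15%, evenly spaced | 0.00125 / 0.0900 | 1.4% | 0.048 |
| Fetal blood sampling | 2 to 20%, evenly spaced | 0.00405 / 0.0979 | 4.1% | 0.045 |
| Internal monitoring | 20 to 45%, evenly spaced | 0.00781 / 0.2194 | 3.6% | 0.046 |
| Internal monitoring | 10 to 60%, evenly spaced | 0.03125 / 0.2275 | 13.7% | 0.035 |

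**3. Simulation check, primary outcome.** These runs used 20,000 trials per scenario, a control risk of 2.8% overall, exact 1:1 allocation within centre, and centre sizes that were also assumed. They compare the unstratified Wald test with the centre-stratified Mantel-Haenszel relative risk.

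| Assumed centre control rates | Type I error, unstratified / stratified | Power, unstratified / stratified |
|---|---|---|
| all equal | 0.049 / 0.049 | 0.821 / 0.821 |
| 1.4% to 4.1% | 0.050 / 0.051 | 0.820 / 0.821 |
| 0.5% to 6.0% | 0.046 / 0.048 | 0.820 / 0.823 |

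In the last row the mean standard error of the log relative risk is 0.1571 unstratified and 0.1561 stratified, a difference of 0.6%. With simple, unblocked randomisation in five centres of 1464, the standard deviation of the log relative risk is 0.1582 unstratified and 0.1578 stratified.

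**4. Simulation check, secondary outcomes.** Simulation with no treatment effect agrees with the table in step 2. At 10 to 60% internal monitoring and exact balance within centre, type I error is about 0.034 unstratified and 0.05 stratified. With unblocked sequences both methods hold about 0.05, and stratifying cuts the variance by about 14%.

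**The case against.** The strongest reply is that the omission is inferred from silence. The Data analysis section does not call the relative risk crude, and a Mantel-Haenszel relative risk stratified by centre is itself a relative risk with a 95% confidence interval. The choice of estimator is a detail that a condensed article often leaves to the statistical analysis plan, which is not shown. This stands, and it limits the point: nothing in the article contradicts the randomisation scheme.

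A second reply is that centre is already in the plan through the subgroup analysis. That shows centre is recorded and will be examined, but separate centre estimates do not make the overall estimate stratified.

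A third is that the effect on the primary outcome is too small to matter. The figures bear this out.

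A reader might also infer that stratifying gives real protection if arms are unbalanced in a centre with an extreme rate. The figures do not support this for acidosis. With 1464 women in a centre and simple randomisation, the share allocated to one arm has a standard deviation of only 0.5/√1464 = 1.3 percentage points. The simulation with simple randomisation already includes such imbalance, and the standard deviation of the log relative risk moved by only 0.0004.

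**Conclusion.** The point holds as a minor one. The analysis as written does not carry the randomisation stratum into the overall relative risk, and the centre subgroup analysis does not fill that gap.

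A reader might go further and conclude that the protocol commits to an invalid or biased crude comparison. The documents do not support that. The word is not used, the unstratified relative risk is valid under 1:1 allocation within centre, and its type I error is at or slightly below 0.05. The sample size is unaffected.

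For metabolic acidosis the gain is about 0.3% to 0.9% of variance with unblocked sequences and none in the estimate with balance within centre. For fetal blood sampling and internal monitoring it may reach about 4% to 14% of variance. With balance within centre, the benefit is instead the correction of an interval that is too wide. These sizes rest on assumed centre rates and centre sizes. The upper secondary-outcome figures need large differences in practice between hospitals.

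**What to change.** Optional. Add one sentence to the Data analysis section: the primary relative risk and the relative risks for binary secondary outcomes are Mantel-Haenszel estimates stratified by centre, each with a 95% confidence interval, and the unstratified relative risk is reported as a sensitivity analysis. If the statistical analysis plan already says this, a cross-reference is enough. The choice is best fixed before the pilot analysis after the first 1500 cases, because that analysis looks at the effect of the alerts. The change needs no extra data, since centre is already recorded, and no new sample size calculation.

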#### Collection of baseline, labour and outcome data

Baseline, labour and outcome data will be obtained by the local research midwife on the next working day after delivery and entered into the Omniview-SisPorto^®^ 3.5 program. Baseline demographic and obstetric data of enrolled women will include maternal age, height, weight; pre-existing or current medical conditions; third trimester group B streptococcus carrier state if known, number of previous pregnancies; number of previous vaginal, instrumental, and caesarean deliveries. Data on the current labour will include gestational age; spontaneous or induced; normal or augmented; presence of slight or thick meconium staining of amniotic fluid; occurrence of fever (temp ≥38°C); use of epidural, parenteral, or inhaled analgesia; other intrapartum medications; result(s) of FBS; date and time of birth; interval between end of fetal monitoring and delivery; normal, instrumental, or caesarean delivery; indication for instrumental or caesarean delivery. Outcome data will include newborn birthweight, sex; 1 and 5-min Apgar scores; umbilical artery pH (3 decimal places), pCO2, bicarbonate, BE_ecf_; umbilical vein pH (3 decimal places), pCO2, bicarbonate, BE_ecf_; neonatal intensive care unit admission and indication. These data will be transmitted in an anonymised format to the co-ordinating centre. Cord acid base data will be assessed for accuracy. If cord blood samples are not available, neonatal data will be used to asses the occurrence of metabolic acidosis.

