#### Secondary outcome measures

The secondary outcomes are: overall rates of caesarean section and of caesarean section for non-reassuring fetal state; overall rates of instrumental vaginal delivery and of instrumental vaginal delivery for non-reassuring fetal state; fetal blood sampling rates; incidence of 5-minute Apgar score < 7; need for neonatal intensive care unit admission; incidence of moderate and severe neonatal encephalopathy with a hypoxic marker; perinatal death; rate of delayed interventions (interval between red alerts - offline analysis in the control arm - and delivery in metabolic acidosis cases); internal FHR monitoring rates; tracing quality and signal loss.

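### For caesarean and instrumental delivery, a relative risk adjusted for centre, parity and previous caesarean would be slightly more precise than the valid but apparently unadjusted comparison that the protocol describes

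*Protocol article*

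**What the plan says.** In the protocol article, Data analysis states the method for the primary outcome: "The incidence of metabolic acidosis will be compared across both groups, using relative risk with 95% confidence intervals". For the rest it says: "A similar methodology will be applied to secondary outcomes". Neither sentence names a covariate or stratification by centre. The section's only remark on baseline factors concerns balance: "Minimal differences between groups are expected in baseline patient characteristics".

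Collection of baseline, labour and outcome data lists, among the baseline items, the "number of previous vaginal, instrumental, and caesarean deliveries". Nulliparity and previous caesarean follow directly from these counts. Under Randomisation, allocation is 1:1 with a separate sequence for each centre.

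Secondary outcome measures opens with operative delivery: "overall rates of caesarean section and of caesarean section for non-reassuring fetal state", followed by the corresponding rates for instrumental vaginal delivery. The article gives no expected rate for either.

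**The concern.** Randomisation makes the groups comparable on average, so an unadjusted relative risk is unbiased. Expected balance is nevertheless not what decides whether adjustment is worthwhile. The gain in precision depends on how strongly a baseline factor predicts the outcome, and it exists even when the groups are perfectly balanced. Parity and previous caesarean are plausible strong predictors of how a woman delivers and much weaker predictors of metabolic acidosis.

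The operative-delivery outcomes carry the other side of the trial's question. The Background notes that CTG monitoring has tended to raise operative delivery rates, and the guidance for red alerts in Table 1 includes delivery among the options to consider. A reader will want to set any fall in acidosis against any rise in intervention, so somewhat narrower intervals for the delivery outcomes are worth having when the data are already there. What is at stake is efficiency, not validity.

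**Working it through.** **1. The plan's own figure.** Sample size works from "assuming a reduction in metabolic acidosis from 2.8% to 1.8%, with an alpha of 0.05, a two-sided test, and a power of 0.80", and the quoted relative risk of 0.64 gives 2.8% × 0.64 = 1.792%. A two-proportion calculation with continuity correction on 2.8% and 1.792% gives 3661 per arm, or 7322 in total, against the stated 7320. Inflation for 10% loss gives 7320/0.9 = 8133.3, against the stated 8133. The sample size thus reproduces as an unadjusted comparison and is not in question.

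**2. Formula for the gain.** Adjusting a marginal relative risk for a baseline factor multiplies the variance of its logarithm by about (1 − R²), where R² is the share of outcome variance that the factor explains. For a two-level factor with share f and outcome rates a and b:

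R² = f(1 − f)(a − b)² / [p(1 − p)], with p = fa + (1 − f)b.

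The standard error falls by 1 − √(1 − R²), and the equivalent sample size is 7320/(1 − R²).

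**3. Inputs.** The 7320 analysable women (3660 per arm) come from Sample size. The nulliparous share (f = 0.55) and all rates by parity are assumptions. With f = 0.55, f(1 − f) = 0.2475.

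**4. Instrumental delivery** (rate in nulliparae / multiparae):

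- 20% / 10%: p = 0.155; R² = 0.2475 × 0.0100 / 0.1310 = 1.9%; standard error 0.9% lower; equivalent to 7461 women.
- 25% / 8%: p = 0.1735; R² = 0.2475 × 0.0289 / 0.1434 = 5.0%; standard error 2.5% lower; equivalent to 7704 women.
- 30% / 6%: p = 0.192; R² = 0.2475 × 0.0576 / 0.1551 = 9.2%; standard error 4.7% lower; equivalent to 8061 women.

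Simulating 40,000 trials of this size, with a parity-standardised against an unadjusted log relative risk and no true effect, gave variance reductions of 1.9%, 5.0% and 9.2%, in agreement with the formula.

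**5. In confidence-interval terms.** With a true relative risk of 1 and 3660 per arm, SE = √[2(1 − p)/(3660p)].

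- 25% / 8%: SE 0.0510; unadjusted 0.905 to 1.105; adjusted 0.907 to 1.102.
- 30% / 6%: SE 0.0480; unadjusted 0.910 to 1.099; adjusted 0.914 to 1.094.

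**6. Caesarean section.** Assume 55% nulliparous, 35% multiparous without caesarean and 10% with a previous caesarean. With group rates of 25.3%, 7.8% and 33.7% (20% overall; odds ratios 4 and 6 against multiparae without caesarean), R² = [0.55 × 0.053² + 0.35 × 0.122² + 0.10 × 0.137²]/0.16 = 0.00863/0.16 = 5.4%, and the standard error is 2.7% lower. Weaker assumptions (odds ratios 2 and 3, 20% overall) give 2.1%. Stronger ones (6 and 12, 25% overall) give about 10%. The order of size is the same as for instrumental delivery.

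**7. Metabolic acidosis.** Rates of 3.0% / 1.5% by parity give R² = 0.2%, and 4.0% / 1.0% give 0.9%. Power at 3660 per arm for 2.8% against 1.8% (no continuity correction) is 81.4% unadjusted, 81.6% at R² = 0.005 and 81.8% at R² = 0.01.

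**The case against.** The strongest case against is that this is a detail a journal article leaves to the full protocol or analysis plan, and that an unadjusted relative risk in a 1:1 randomised trial is valid. Both statements are correct. The point survives only as a suggestion for improving a stated method. If the full plan already lists covariates, it is settled.

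The size of the gain is a second fair objection. On the assumed rates, confidence limits move by about 0.002 to 0.005. No reading of benefit against intervention would turn on that, the secondary aims are only to quantify intervention rates, and the trial is not sized on them. What remains is that the gain is nearly free.

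Three stronger readings are tempting, and the article does not support them.

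- A reader might infer that the plan rejects adjustment because the groups will be balanced. The text only expects small baseline differences. It never uses the word unadjusted, and an adjusted relative risk would also fit its wording.
- A reader might infer that every outcome is affected. The reference to a similar methodology is loose, and the secondary list ends with "internal FHR monitoring rates; tracing quality and signal loss", some of which need not be proportions. The interval from red alert to delivery need not be one either.
- A reader might add gestational age to the covariates. It is recorded ("Data on the current labour will include gestational age"), but nothing in the documents or in the calculation above shows what it would contribute.

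It is also fair to object that one multi-covariate model for all binary outcomes would be unwise. Perinatal death and moderate or severe encephalopathy may have too few events for a stable fit.

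**Conclusion.** The point holds as a minor efficiency suggestion confined to caesarean section and instrumental vaginal delivery. The planned analysis contains no error, the sample size reproduces, and the primary result would not change in any practical way. That the comparison is unadjusted is an inference from the absence of any named covariate. For instrumental delivery the expected gain is a variance about 2-9% lower and a standard error about 1-5% lower, equivalent to about 140-740 further women on top of 7320 (7461 − 7320 = 141; 8061 − 7320 = 741). This rests on the assumed 55% nulliparous share and the assumed rates of 20-30% and 6-10%. With weaker prognostic factors the gain would be smaller still.

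**What to change.** For caesarean section and instrumental vaginal delivery, pre-specify a marginal relative risk with 95% confidence interval, from a modified Poisson model with robust standard errors or a logistic model with standardisation. Adjust for centre, nulliparity and previous caesarean, and report the unadjusted relative risk alongside. Keep the planned relative risk for metabolic acidosis and the rare outcomes.

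Restrict the covariates to factors fixed before randomisation. The data-collection section lists epidural use, fever, meconium and augmentation close to the baseline items, and these can arise after allocation, so they should not enter the model. Because data are entered after delivery, previous deliveries should be taken from records made before randomisation, and a simple rule for a missing covariate should be stated. The choice should be written down before the pilot analysis at 1500 women, since that analysis looks at the effect of the alerts.

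Cost: a few lines in the analysis plan and slight extra analysis work, with no new data.
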